## **10.4 Interim analysis**

Interim analysis will take place when 1/3 (168 cases) and 2/3 (336 cases) have completed 3-month follow-up. The O'Brien-Fleming boundaries will be used at the interim analysis as follows:

There are no established techniques for the assessment of interim trial efficacy boundaries using an ordinal logistic regression model (proportional odds model). Instead, we will revert to a simple dichotomous analysis of the mRS score at 0-2 defined at 90 days from randomization. The Z-statistic for this analysis shall be derived from the normal approximation of the binomial distribution as an unadjusted two-sample test of proportions. For an RCT comparing two treatment groups with respect to a binary outcome and two interim analysis, corresponding

significance levels based on the O'Brien & Fleming boundary are two-sided 0.0002 (stage 1), 0.0123 (stage 2) and 0.046 (stage 3, final analysis).

With the result of interim analysis, DSMB will make the decision to continue or halt the study according to the test boundaries. The study will stop prematurely for futility if the result from the interim analysis indicate that we can't achieve an effective conclusion with the current sample size. Premature stopping for early success will be achieved if the interim analysis result has already proved the effect of intervention at significance level. Otherwise, the study will be continued until the predefined termination date. In interim analysis, the final sample size is allowed to be adjusted if the estimation of the primary outcome is drastically different from the actual data.

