### ● Executive committee

The executive committee is responsible for reviewing the status of the trial and available blinded data and will take appropriate actions regarding the conduct of the study. Executive Committee meetings will be organized to make major decisions. The composition of the Executive Committee and its responsibilities are described in a charter which will be finalized before the start of the trial.

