## **6. Sample size estimates**

In this study, a multicenter, open, randomized, parallel control design method was used. The primary measure of efficacy was mRS score at 90±7 days after enrollment (considered as ordered variable). According to the literature data and clinical experts' opinions, the parameters were set as follows: (1) The proportion of mRS score 0-6 in control group was 3%, 4%, 10%, 17%, 16%, 12% and 38%, respectively; (2) The average treatment effect of EVT improved the outcome with the common OR value for improvement of mRS reached 1.73; (3) Two Interim analysis were considered. Adjusted level  $\alpha=0.046$  (two-sided) and power  $1-\beta=0.90$ . (4) The sample size was allocated to the intervention group and the control group in a 1:1 ratio. Based on these parameters, the total sample size was 452. Considering 10% attrition rate, the final total sample size was 502 cases, 251 cases in each group.

Interim analysis will take place when 1/3 (168 cases) and 2/3 (336 cases) have completed 3-month follow-up. O'Brien-Fleming boundaries will be used at the interim analysis as follows:

There are no established techniques for the assessment of interim trial efficacy boundaries using an ordinal logistic regression model (proportional odds model). Instead, we will revert to a simple dichotomous analysis of the mRS score at 0-2 defined at 90 days from randomization. The Z-statistic for this analysis shall be derived from the normal approximation of the binomial distribution as an unadjusted two-sample test of proportions. For an RCT comparing two treatment groups with respect to a binary outcome and two interim analysis, corresponding significance levels based on O'Brien & Fleming boundary are two-sided 0.0002 (stage 1), 0.0123 (stage 2) and 0.046 (stage 3, final analysis).

With the result of interim analysis, DSMB will make the decision to continue or

---

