## 10. Data handling conventions

### Premature Withdrawal and Missing Data

If any subject withdraws prematurely from the study (prior to the final visit D90±7 days assessment), they are required to complete the withdrawal visit in the CRF. The reasons for withdrawal will be presented in a summary table. For the purposes of summaries and analysis of clinic visit data, this visit will be assigned to the next scheduled clinic visit for that subject, regardless of whether the date falls within the next visit window.

Subjects who withdraw before the end of the study, but who do provide at least one post-baseline measure for a particular endpoint, will be included in the analysis. Subjects who do not attend any visits after randomization will be excluded from analysis of any endpoint, as no post-baseline data will be available.

Outlier values will be evaluated for their validity; all data will be included unless judged to be invalid (e.g., deemed incompatible with life by Medical Monitor and/or deemed invalid by the DSMB).

Efforts will be undertaken at study sites to reduce the amount of missing data. Due to the severity of the condition and the short 90-day follow-up period, very little loss to follow-up is anticipated. For the primary efficacy endpoint, complete data will be used and missing data will not be imputed in the main analysis. Also, sensitivity analyses with missing data imputed by LOCF (Last Observation Carry Forward) and WCCF (Worst Case Carry Forward) methods will be undertaken to explore the effect of missing data on the endpoint and test the robustness of the estimate.

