### **36h (24-48h) infarct volume change (by CT or MRI)**

The change of 36h (24-48h) infarct volume change (by CT or MRI) will be analyzed using student t-test or Wilcoxon rank sum test as appropriate.

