## 十六、 数据安全监查

制定相应的数据安全监察计划,所有 AE 均详细记录,恰当处理并追踪直到妥善解决或病情稳定,按照规定及时向伦理委员会、主管部门、申办者和监督管理部门报告 SAE 与非预期事件等;主要研究者定期对所有 AE 进行累积性回顾,必要时召开研究者会议评估研究的风险与受益;本研究将建立独立的数据安全监察委员会对累积的安全性数据以及有效性数据进行监查,以做出研究是否继续进行的建议。

临床试验过程中,受试者的数据应以匿名方式收集在 CRF 上,受试者只有通过受试者编号和姓名拼音缩写来辨认。由于安全或行政指令原因,例外知道受试者身份时,和研究者应共同承担保密责任。知情同意书允许患者同意已授权的申办方、伦理委员会、权威机构直接查阅 CRF 上相关的原始资料(如患者的医疗档案、预约记录、原始实验室记录等)。上述人员应遵循职业保密规定,必须对患者的所有个人身份信息或医疗信息保密。

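### The SAP names the DSMB, which probably knows the comparative interim results, as a body that may declare outlier values invalid, with no criterion and no blinding requirement

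*Supplement*

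**What the plan says.** The rule is in SAP v2.0, section 10 (Data handling conventions), under premature withdrawal and missing data: "Outlier values will be evaluated for their validity; all data will be included unless judged to be invalid". A parenthesis then gives examples of such a judgment: "deemed incompatible with life by Medical Monitor and/or deemed invalid by the DSMB".

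The Medical Monitor's ground has some substance, since the value must be physiologically impossible. The DSMB's ground is only that the DSMB says so. The section does not say which endpoints are covered, when the judgment is made, or whether the person making it knows the arm. It asks for no listing of excluded values.

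On the DSMB's other work, protocol V7.1, section 10.4, says: "With the result of interim analysis, DSMB will make the decision to continue or halt the study according to the test boundaries". SAP v2.0, section 6, repeats this and describes the interim statistic, on 90-day mRS 0-2, "as an unadjusted two-sample test of proportions".

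For infarct volume change, SAP v2.0, section 12, says the endpoint "will be analyzed using student t-test or Wilcoxon rank sum test as appropriate".

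**The concern.** Whether a recorded value is valid should be decided by people who know neither the patient's arm nor how the comparison is going. Otherwise the decision can be influenced, even unintentionally, by its effect on the result. A body that has seen a comparison between the arms is poorly placed to make it, and being asked to do so blurs its monitoring role.

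The trial is open-label and relies on blinded endpoint assessment for its credibility. A rule that lets a probably results-aware body set aside a blindly assessed value runs against that design.

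**Working it through.** The plan states no figure on this point, so the check is mainly a reading of the passages together.

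**1. Does the DSMB know comparative results?**
- It decides on continuing or stopping by comparing a two-arm test with the boundaries (protocol V7.1, section 10.4; SAP v2.0, section 6). It cannot apply the boundaries without the result of that test.
- Section 16 of the Chinese-language protocol, which carries the same 502-patient plan, says: "本研究将建立独立的数据安全监察委员会对累积的安全性数据以及有效性数据进行监查". That is, an independent board monitors accumulating safety and efficacy data. Section 16 of English V7.1 mentions review of safety data only.
- Protocol V7.1, section 13.1, says of another body: "The executive committee is responsible for reviewing the status of the trial and available blinded data". It sets no such limit for the DSMB.

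Knowledge of the interim comparison is thus a strong inference. Knowledge of individual allocation is possible but not stated.

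**2. Does anything else require a blinded validity judgment?** I found no such requirement in the current protocol or SAP. Protocol section 10.3 wants the SAP issued before lock and before the code is broken, but that does not govern later decisions on single values. The LOCF and WCCF analyses in SAP section 10 handle missing values of the primary endpoint. They would not restore an observed value that had been struck out.

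**3. Which endpoints could be touched?**
- *mRS (primary).* The scale runs from 0 to 6 and every score is admissible. The planned control distribution puts 38% at 6, the most frequent category, so a death cannot sensibly be called an outlier.
- *Infarct volume change (secondary).* This is continuous, may have extreme values, and may be compared by t-test.
- *Laboratory values and similar data.* These are also within the wording.

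**4. Scale for infarct volume.** Removing k values that lie d ml from the arm mean, out of n, moves that mean by k × d / (n − k). Assume n = 452 / 2 = 226, k = 3, and d from 100 to 300 ml; k and d are not in the documents.
- d = 100: 3 × 100 / 223 = 1.3 ml
- d = 300: 3 × 300 / 223 = 4.0 ml

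Protocol section 1.1 cites infarct growth of 44 ml against 98 ml in a cohort with large cores, a difference of 54 ml. The shift is 1.3 / 54 = 2% to 4.0 / 54 = 7% of that. The documents give no standard deviation, so it cannot be converted into a p-value or an error rate.

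**5. Is the DSMB needed for this task?** No. Under protocol section 10.2.5 the data administrator corrects obvious errors and sends other queries to the sites. Images are read centrally by readers unaware of treatment, EVT angiography excepted (section 3.4), and the imaging assessment committee confirms results before entry (section 5.3).

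**The case against.** The strongest reply is that this is one parenthesis, introduced as an example, inside a rule whose default is inclusion. It gives the DSMB no duty to screen outcomes, and routine cleaning bypasses the DSMB. The endpoint most exposed is already read blind and confirmed by committee. The specified interim test concerns mRS 0-2, and no sentence sends infarct volume by arm to the DSMB. All of this stands and keeps the point small. It does not remove it, because the sentence still names the DSMB, without criterion or blinding, as able to have a value excluded.

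Three stronger readings are tempting, and the documents do not support them.
- *That the DSMB is unblinded as a matter of record.* No passage says so. Its charter is not shown, and arms may be coded.
- *That the primary result is at risk.* One can calculate how a borderline ordinal result would move if deaths were dropped from one arm, but only by treating mRS 6 as an outlier, which the sentence does not plausibly reach.
- *That the false-positive rate for infarct volume rises by a stated amount.* Such a figure needs an assumed standard deviation, several very extreme values, and removal always from the same arm in the same direction. It would describe deliberate misuse, and nothing in the plan points to that.

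**Conclusion.** The point holds in limited form. The current SAP names a body that can be inferred to know comparative results as one that may declare outlier values invalid, with no written criterion and no requirement of blinding. This permits results-aware exclusion, chiefly of continuous secondary data such as infarct volume change. The primary mRS analysis is unlikely to be affected.

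The conclusion rests on one inference: that applying the boundaries, and reviewing efficacy data as the Chinese text describes, means the DSMB sees the comparison. If the charter keeps the DSMB out of data decisions, the SAP sentence conflicts with the charter and should still go.

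This is a free improvement rather than a defect that threatens the trial's conclusion. The open choice between t-test and Wilcoxon test is a separate matter and does not follow from this clause.

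**What to change.** In SAP section 10, strike the DSMB alternative from the parenthesis. Add that data management settles questions of validity, with the core lab doing so for images, blinded to allocation and before database lock. The Medical Monitor example can stay under the same condition. Require a listing, by arm, of every value excluded as invalid, with the reason.

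The cost is one or two SAP sentences and one listing. The cleaning route and the blinded central reading already exist; what is new is the explicit blinding and timing. Sample size, endpoints and the DSMB's monitoring role do not change.

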### **9.5.3 Follow-up and risk management**

The Investigator should take all appropriate measures to ensure the safety of the patients.

Screening of subjects should strictly follow the inclusion and exclusion criteria of the study. If an AE occurs during the study period, relevant evaluations will be performed, including blood routine examination, coagulation, creatinine, hepatic function, renal function, arterial blood gas analysis, ultrasound and computer tomography. Targeted treatment and necessary consultation should be carried out in a timely manner. When dealing with SAEs, it is important to make sure patient's airway is clear, respiration, blood pressure and heart rate is steady.

Notably, the investigator should follow up the outcome of any AEs (clinical signs, laboratory values or other, etc.) until the patient's condition returns to normal or stabilizes. The follow-up will continue even if the patient withdraws from the clinical trial, and the patient will be interviewed by telephone or face-to-face at the scheduled visit time. The monitoring team may request additional visits and investigations.

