## **10. Statistical Analysis**

### **10.1 Sample size estimation**

In this study, a multicenter, open, randomized, parallel control design method was used. The primary measure of efficacy was mRS score at 90 days ( $\pm 7$  days) after enrollment (considered as ordered variable). According to the literature data and clinical experts' opinions, the parameters were set as follows: (1) The proportion of mRS score 0-6 in control group was 3%, 4%, 10%, 17%, 16%, 12% and 38%, respectively; (2) The average treatment effect of EVT improved the outcome with the common OR value for improvement of mRS reached 1.73; (3) Two Interim analysis were considered. Adjusted level  $\alpha=0.046$  (two-sided) and power  $1-\beta=0.90$ . (4) The randomization was allocated to the intervention group and the control group in a 1:1 ratio. Based on these parameters, the total sample size was 452. Considering 10% attrition rate,

the final total sample size was 502 cases, 251 cases in each group.

Interim analysis will be conducted when 1/3 (168) and 2/3 (336) of patients have completed 3-month follow-up. The O'Brien-Fleming boundaries will be used at the interim analysis with a two-sided alpha of 0.0002 (stage 1), 0.0123 (stage 2) and 0.046 (stage 3, final analysis).

The PASS software (NCSS, LLC, version 11) was used to calculate the sample size.

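### The main analysis of 90-day mRS is complete-case: harmless at the loss the SAP expects, but biased if the 10% attrition allowance falls unevenly by arm, and the missing-data rules conflict

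*Supplement*

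**What the plan says.** SAP v2.0, section 10 (Premature Withdrawal and Missing Data), sets the main analysis: "For the primary efficacy endpoint, complete data will be used and missing data will not be imputed in the main analysis". It adds that "sensitivity analyses with missing data imputed by LOCF (Last Observation Carry Forward) and WCCF (Worst Case Carry Forward) methods will be undertaken", and its premise is that "very little loss to follow-up is anticipated". Section 6 nevertheless allows for loss: "Considering 10% attrition rate, the final total sample size was 502 cases, 251 cases in each group".

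Three further rules stand in the same part of section 10:
- Withdrawn subjects stay in if they leave early "but who do provide at least one post-baseline measure for a particular endpoint, will be included in the analysis".
- For a withdrawal visit, "this visit will be assigned to the next scheduled clinic visit for that subject, regardless of whether the date falls" inside that visit's window.
- Subjects seen at no visit after randomization are left out of every endpoint. Section 7, by contrast, puts all randomized subjects in the full analysis set (FAS) and bases the primary analysis on it.

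In protocol V7.1, Appendix Table 1 scores death as mRS 6. Sections 8.3, 8.4 and 8.6 collect mRS at day 7 or discharge and at day 30, and NIHSS at 36 hours and day 7. Section 9.5.3 says: "The follow-up will continue even if the patient withdraws from the clinical trial, and the patient will be interviewed by telephone or face-to-face".

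**The concern.** Death is a category of the primary scale, so a known death cannot be missing. Dropping patients without a day-90 score therefore removes mainly scores 0 to 5 and keeps the 6s. The arm that loses more patients looks worse, even if loss is random among survivors. Patients and treating physicians know the allocation (protocol 3.4), so loss could differ by arm. Belonging to the FAS does not help a patient whom the model omits for want of a score. Earlier mRS and NIHSS values that would predict the missing scores are collected, but the main model does not use them.

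A second problem arises at any loss rate. The section 10 rules allow two readings for a patient who withdraws after day 30. The withdrawal-visit score may be entered as day 90, or the patient may be dropped as incomplete. Two analysts could follow the SAP and build different primary datasets.

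**Working it through.** **Inputs from the plan.** Control mRS 0 to 6: 3, 4, 10, 17, 16, 12 and 38%, so 62% survive. Common OR 1.73, final two-sided alpha 0.046, power 0.90, 251 per arm (SAP v2.0 section 6).

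**The plan's own figure.** Whitehead's proportional-odds formula is N = 12(z₁ + z₂)² / [(ln OR)² (1 − Σp̄³)]. With z₁ = 1.995, z₂ = 1.282, ln 1.73 = 0.548 and 1 − Σp̄³ = 0.952, N = 450.3 against the stated 452. Then 452/0.9 = 502.2, against 502. The sample size reproduces.

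**How the bias arises.** Suppose there is no effect, all deaths are recorded, and 5% of the EVT arm and 15% of the BMM arm are lost at random among survivors. Among patients with a score, mortality is 38/(100 − 5) = 40.0% on EVT and 38/(100 − 15) = 44.7% on BMM, although true mortality is equal.

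**Size.** I fitted the proportional-odds model to the expected counts. Rejection uses Whitehead's information V = n₁n₂/(3N) × (1 − Σp̄³). For 5%/15% under the null, OR = 1.167 and V = 34.3, so the expected z is ln(1.167) × √34.3 = 0.906. Rejection is Φ(0.906 − 1.995) + Φ(−0.906 − 1.995) = 0.138 + 0.002, about 14%. Other splits, as % of all randomized (all assumed, because the documents give no loss by arm):

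| Lost EVT / BMM | OR, true 1.00 | Two-sided rejection | OR, true 1.73 |
|---|---|---|---|
| 1 / 2 | 1.01 | 4.7% | 1.76 |
| 2 / 5 | 1.04 | 5.2% | 1.81 |
| 10 / 10 | 1.00 | 4.6% | 1.78 |
| 5 / 15 | 1.17 | about 14% | 2.03 |
| 15 / 5 | 0.86 | about 14% | 1.57 |

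For 15/5 under OR 1.73, V = 35.4 and z = ln(1.572) × √35.4 = 2.69, so power is Φ(2.69 − 1.995) = 0.76. With all 502 scores observed it is 0.93.

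**If some lost patients died unrecorded.** The null bias at 5/15 falls from 1.17 to 1.09–1.13.

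**Planned sensitivity analyses, 5/15 under the null.** LOCF from day 30 gives about 0.97–1.02. WCCF read as mRS 6 makes apparent mortality 43% against 53% and gives OR 1.41, further from the truth than complete-case.

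**Imputation from day-30 mRS within arm, 5/15.** This comes from a simulation with 400,000 patients per arm. It assumes a latent day-30/day-90 correlation of 0.85 and 60–90% of deaths by day 30.
- Loss at random among survivors, or dependent on day-30 mRS: imputation given survival returns 1.00 and 1.73. Ignoring survival leaves 1.01–1.05 under the null.
- Some deaths unrecorded: treating every lost patient as a survivor overshoots, to about 0.96–0.98 under the null. Imputing without that restriction gives about 1.00. The rule for unknown vital status therefore matters.
- Survivors with good day-90 scores lost more often (MNAR): under the null the OR is 1.07, against 1.31 complete-case. Under a true 1.73 it is 1.90, against 2.36.

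**The case against.** The strongest reply is that the SAP expects very little loss, and at that level nothing happens. The 10% is a sample-size allowance with no split by arm, and equal loss leaves the null OR at 1.00. All of this stands. It is why the point is a cheap improvement and does not show that the primary result will be wrong.

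A reader might infer that only survivors can be missing. The documents do not support that. Day 90 is a telephone visit (protocol 3.3), an unreachable patient may have died, and the SAP has no rule for unknown vital status. A reader might also infer that imputation removes the bias. It does so only if loss is at random given the collected data and vital status is handled correctly. Nor do the documents say that families in the BMM arm will leave more often; that is conjecture.

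The SAP does have safeguards. LOCF uses the earlier scores and would tend to expose the problem, and section 11 reports withdrawals by arm. Neither changes the main estimate, and WCCF can mislead.

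On withdrawals, protocol 9.5.3 speaks in the context of adverse-event follow-up and does not say that mRS is collected. The relabelling rule refers to clinic visit data, so its reach to a telephone mRS is unclear. That unclarity supports reconciling the text; it does not prove that earlier scores will be entered as day 90.

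**Conclusion.** The point holds as a change that should be made, at low cost. The main analysis is complete-case on a scale where recorded deaths are never missing, so its validity depends on loss being small or balanced. The bias is negligible at 1%/2% loss (OR 1.01). It is material at an assumed 5%/15% (OR about 1.17 and about 14% rejection under the null, somewhat less with unrecorded deaths), and the reverse split reduces power to about 0.76. These figures assume loss at random among survivors and a split that the documents neither state nor predict. A reader should not conclude that the type I error of this trial is 14%. The inconsistency among the section 10 rules depends on no such assumption.

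**What to change.** 1. Analyse all FAS patients. Score recorded deaths as 6 and use the actual day-90 score wherever one is obtained, including after withdrawal.
2. Multiply impute the remaining 90-day scores within arm, conditional on last known vital status. Use day-30 and day-7 mRS, 36-hour and day-7 NIHSS and baseline variables, and combine results by Rubin's rules. Use the same imputations for mRS 0-2 and 0-3.
3. State how unknown vital status at day 90 is handled.
4. State that a withdrawal-visit mRS is not entered as day 90. Reconcile this with the rules on partial data, on subjects without any visit and on the FAS.
5. Keep complete-case as a sensitivity analysis and add a delta or tipping-point (MNAR) analysis. If WCCF stays, define the worst case.

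The cost is SAP wording, one imputation step in SAS and one further sensitivity analysis. The downside is a stated missing-at-random assumption; if loss is MNAR, imputation reduces the bias without removing it. If loss proves very small, the result will hardly change.
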